#### Pilot study/feasibility

A pilot study will be carried out to estimate the number of couples required for initial screening, attrition rate, and the rate of reduction in postoperative depression. This pilot study will be performed on 50 infertile women. After obtaining informed consent, the couple’s depression level will be measured using a standard questionnaire.

The sample size required for initial screening in the field is estimated based on the prevalence of mild to moderate depression. Furthermore, to assess feasibility, after receiving informed consent, the intervention will be performed on couples who are eligible for research, and their level of depression will be measured for the second time. The depression levels at the first and second assessments will be compared by the research supervisor. If the level of depression would be increased in the second assessment, the trial will be stopped.

If any problems are identified in the implementation of the intervention, the necessary changes will be applied by the research team after reaching a consensus. Couples participating in the pilot study will not participate in the clinical study, and the results of the measurements will not be included in the analysis.

#### Sample size

The sample size will be calculated for a 1:1 allocation ratio, considering presumed depression score reduction after the intervention, estimated sample loss, and 95% confidence level.

#### Recruitment

Couple’s eligibility assessment and screening will be performed by the Ph.D. candidate in reproductive health. During the first interview, X infertile couples will be invited, and the levels of depression, anxiety, stress, and infertility adjustment will be evaluated using validated questionnaires. After determining the eligible couples, X couples will be randomly selected and invited by the researcher to participate in the study. The study objectives and the way of participating in the study will be explained to couples who accept the invitation.

The informed consent will be obtained from eligible couples by a legal advisor in the infertility center. The representative of the Ethics Committee of the Isfahan University of Medical Sciences will supervise all stages of the research and will decide to end the trial.

#### Sampling and data collection

After determining the eligible couples, X couples will be randomly selected by the researcher. To randomly assign the couples to the intervention and control groups, X closed envelopes containing blue and green cards will be prepared. The couples will be referred to the midwife consultant and receive one of the envelopes and complete demographic characteristics.

The midwife and participants will be blinded to the study group. After random allocation, one researcher, who will not be involved in sampling and random allocation, will assign each group’s card color. Couples’ depression, anxiety, stress, and infertility adjustment levels will be evaluated using valid questionnaires 2 and 3 months after starting the intervention and compared between the groups (Table 1).

**Table 1 Tab1:** Schedule for data collection during the trial

Time point	Study period				
	Enrollment	Allocation	Post allocation		Closeout
	Pre-baseline	Baseline	Time 1	Time 2	
Enrollment					
Eligibility screen	X				
Informed consent	X				
Allocation		X			
Participant characteristics					
Demographics		X			
Infertility profile		X			
Interventions					
Couple-based coping strategies		X			
Solution-oriented counseling		X			
Outcomes assessment					
Depression			X	X	X
Anxiety			X	X	X
Stress			X	X	X
Infertility adjustment			X	X	X

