#### Intervention

The intervention will begin before starting medical treatment. The counselors will be MSc holders in psychological counseling. They will be trained in the developed couple-based coping strategies using face-to-face education and a role modeling approach.

For the intervention group, a counseling psychologist will be educated on the developed couple-based coping strategies based on the color chosen for one group (intervention group) and solution-oriented counseling for the other group (control group).

The number, duration, and intervals of the sessions for intervention and other educational intervention (control) groups will be set identically. It is estimated that the counseling program will be scheduled 3 to 5 times once or twice each week. The researchers will bear the intervention and transportation costs for both intervention and control groups. Participants should not participate in any other research during the intervention. The research is expected to proceed without any harm; however, in case of harm, the main researcher will be responsible for compensating for the reparable harm.

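### The meaning of the two card colours is assigned after the groups exist, with no chance mechanism stated and no bar on seeing baseline data, so the labelling step is open to discretion

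*Protocol article*

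**What the plan says.** The order of events is in three sections of the protocol article, all in the third phase.

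- **Recruitment.** At the first interview "the levels of depression, anxiety, stress, and infertility adjustment will be evaluated using validated questionnaires". These are the variables that later serve as outcomes.
- **Sampling and data collection, allocation.** "To randomly assign the couples to the intervention and control groups, X closed envelopes containing blue and green cards will be prepared". Couples then see the midwife consultant, where they "receive one of the envelopes and complete demographic characteristics".
- **Sampling and data collection, blinding and colour step.** "The midwife and participants will be blinded to the study group". The next sentence reads: "After random allocation, one researcher, who will not be involved in sampling and random allocation, will assign each group’s card color".
- **Intervention.** The counselling psychologist is trained in the two programmes "based on the color chosen for one group (intervention group) and solution-oriented counseling for the other group (control group").

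The article uses the language of randomness for selecting couples and for the envelopes. For linking colour to programme it speaks only of assigning and choosing.

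**The concern.** The envelopes decide which couples share a colour. They do not decide which colour receives the couple-based coping strategies. That second step is placed after the groups are formed, when depression, anxiety, stress, adjustment and demographic data exist for both colours. The one stated safeguard is that the researcher who sets the link takes no part in sampling or allocation. That separates duties but does not blind this person to the data, and the blinding statement names only the midwife and the participants.

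Two randomly formed groups almost always differ a little at baseline. If the labels may be attached with that difference in view, the better-looking group can be named intervention. The direction of the chance imbalance is then no longer random with respect to treatment. At stake is a modest tilt of the comparison of final means towards the new programme.

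**Working it through.** The plan gives no figure to reproduce: numbers of couples are written as X, and no power or effect size is stated. The calculation below only sizes the worst case.

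**Inputs from the protocol article**
- Equal groups: "The sample size will be calculated for a 1:1 allocation ratio" (Sample size).
- Significance level 0.05, from "estimated sample loss, and 95% confidence level" (Sample size). Two-sided testing is assumed, because sidedness is not stated.

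**Assumptions**
- No true treatment effect.
- Correlation ρ between baseline and final score of 0.3 to 0.9.
- Equal SDs at both times.
- 30 per group, treated as independent units (50 shown for comparison).
- Worst case: the colour with the better mean baseline is always named intervention, and the final means are compared without adjustment.

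**Step 1: baseline advantage.** The SE of a difference of two means is √(2/n) SD, which is √(2/30) = 0.258 SD or √(2/50) = 0.200 SD. Always taking the favourable direction gives an expected advantage of SE × √(2/π) = 0.798 × SE, that is 0.206 SD (n = 30) or 0.160 SD (n = 50).

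**Step 2: bias in the final mean.** Only the correlated part carries forward, so bias = ρ × 0.798 × SE. For ρ = 0.5 and n = 30 this is 0.5 × 0.206 = 0.103 SD.

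**Step 3: error rates.** Let Zb and Zp be the standardised baseline and final group differences, bivariate normal with correlation ρ, signed so that positive favours the group named intervention. False favourable results are P(Zp > 1.96 | Zb > 0) = 2 × P(Zp > 1.96 and Zb > 0). False unfavourable results use Zp < −1.96.

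| ρ | False favourable | False unfavourable | Two-sided total | Bias (SE) | Bias, n = 30 (SD) | Bias, n = 50 (SD) |
|---|---|---|---|---|---|---|
| 0 | 2.5% | 2.5% | 5.0% | 0 | 0 | 0 |
| 0.3 | 3.8% | 1.2% | 5.0% | 0.24 | 0.06 | 0.05 |
| 0.5 | 4.5% | 0.5% | 5.0% | 0.40 | 0.10 | 0.08 |
| 0.7 | 4.9% | 0.1% | 5.0% | 0.56 | 0.14 | 0.11 |
| 0.9 | 5.0% | 0.0% | 5.0% | 0.72 | 0.19 | 0.14 |

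The total does not move, because swapping labels leaves a two-sided p-value unchanged. The favourable share cannot exceed 2 × 2.5% = 5.0%. The ρ = 0 row also gives the result when the link is fixed beforehand, drawn at random, or chosen without knowledge of the groups: 2.5% and no bias.

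**Step 4: change scores.** The Outcomes section also names the magnitude of change. With equal SDs, a better baseline shifts the change by (1 − ρ) times the baseline difference *against* the intervention. At ρ = 0.5 and n = 30 that is 0.5 × 0.206 = 0.103 SD.

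**The case against.** The strongest reply is that the article is condensed and does not say how the colour is chosen. A coin toss or a sealed key would fit both sentences. That stands. A reader might infer that the label is in fact picked without randomisation, or that someone means to exploit it, and the documents support neither. What the article does state is the sequence, and nothing in it removes the discretion.

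The design also contains real protection. The couples are split by closed envelopes, and colours without meaning during enrolment help concealment. The screening is done by the Ph.D. candidate and the demographics are collected at the midwife visit, so the researcher who sets the colours is not described as holding these data. Bias needs both access and use of it. This lowers the risk but does not close the gap.

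A reader might carry the full 0.16–0.21 SD into the 3-month means. That is a baseline difference. It shrinks by ρ in the final score and works the other way on change, so one label choice cannot favour both measures. The Data management and analysis section also prescribes ANCOVA with the enrolment score as covariate when enrolment measurements differ, plus adjustment for differing confounders. That partly covers the problem. Because it is conditional, an imbalance not judged different can stay unadjusted.

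A reader might also infer that the rule fails on timing, with early couples waiting while their screening scores age. Recruitment and Sampling can be read as one batch: screen, determine who is eligible, select, hand out envelopes. No accrual period is given, so that failure is not shown.

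Finally, fixing the key early has a cost of its own. With two permanent colours, one leak during enrolment reveals every later allocation. This stands, and the fix takes account of it.

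**Conclusion.** The point holds in a limited form. The article places the colour-to-programme link after group formation, names no chance mechanism, and does not keep the person who sets it from baseline data or group composition. This is a weakness in a stated procedure, not evidence of misuse, and the couple-level randomisation is intact.

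The harm is bounded. In the worst case defined above, false favourable results at most double, from 2.5% to 5.0%, and expected bias in the final mean is about 0.06–0.19 SD at 30 per group. These figures rest on an assumed group size and assumed correlations, because the article gives neither. Consistent ANCOVA would largely remove the effect for measured baseline scores. If the label is set in ignorance of the groups, nothing is lost. The change is worth making because the remedy costs almost nothing.

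**What to change.** In Sampling and data collection, state that the link between colour and programme is set by a documented random draw (coin toss or computer), made by the independent researcher without access to baseline data or group composition. State also when it is made. Either of two times is acceptable:

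- drawn and sealed before the first envelope is opened; or
- drawn once the batch of couples has been allocated.

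In Intervention, reword the reference to the chosen colour so that it means the colour so drawn.

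The cost is protocol wording, with no added staff, visits or participants. There is one small downside: if counsellors learn the key while enrolment continues, a leak would reveal later allocations. The text should therefore say that the key is kept from everyone who enrols couples or hands out envelopes. Drawing after the batch is allocated avoids that exposure.

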#### Intervention

The intervention will begin before starting medical treatment. The counselors will be MSc holders in psychological counseling. They will be trained in the developed couple-based coping strategies using face-to-face education and a role modeling approach.

For the intervention group, a counseling psychologist will be educated on the developed couple-based coping strategies based on the color chosen for one group (intervention group) and solution-oriented counseling for the other group (control group).

The number, duration, and intervals of the sessions for intervention and other educational intervention (control) groups will be set identically. It is estimated that the counseling program will be scheduled 3 to 5 times once or twice each week. The researchers will bear the intervention and transportation costs for both intervention and control groups. Participants should not participate in any other research during the intervention. The research is expected to proceed without any harm; however, in case of harm, the main researcher will be responsible for compensating for the reparable harm.

#### Outcomes

The outcome will be the mean score of depression, anxiety, stress, and infertility adjustment and the magnitude of their change on enrollment and 3 months after starting the intervention in couples in the intervention group compared with those in another educational intervention (as the control group).

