### Third phase: a randomized field trial study

#### Participants and setting

This parallel-group, double-blind, controlled, randomized field trial, superiority framework with an allocation ratio of 1:1 will be conducted on infertile couples who underwent infertility treatment in Isfahan Fertility and Infertility Center, Isfahan, Iran. Couples, at least one of whom suffers from mild to moderate depression, will be invited to participate in the quasi-experimental study. The inclusion criteria will include no history of severe mental disorders and no stressful event during the last 3 months. The exclusion criteria will be a stressful event or the onset of assisted reproductive treatment during the intervention and ovarian hyper-stimulation syndrome due to ovarian induction.

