#### Data management and analysis

Data will be analyzed using the SPSS 19 software and statistical tests, including the independent *t*-test, pair *t*-test, chi-square, and repeated measures analysis of variance (RM ANOVA). If the measurements at the enrollment phase appear differently in the groups, analysis of covariance (ANCOVA), controlling for baseline data and independent variables (group as a fixed parameter and enrollment mean scores as a covariate), will be used. Also, the baseline value of outcome variables and potential confounding variables which are different between the two groups will be adjusted to avoid potential risk of bias and detect independent results. The data normality will be evaluated through the Kolmogorov-Smirnov test. If the data are not normally distributed, nonparametric tests such as Wilcoxon will be used. In the case of missing data, we will utilize the last value carried forward method to impute missing values.

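### Four unranked scales, each as score and as change, form the single outcome of a superiority trial built on depression, so no designated result decides superiority

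*Protocol article*

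**What the plan says.** The Outcomes section defines one outcome: "The outcome will be the mean score of depression, anxiety, stress, and infertility adjustment and the magnitude of their change", from enrollment to 3 months after the start of the intervention, in one arm against the other. The objectives at the end of the Background cover the same four scales in two items: the three DASS-21 scales in one, infertility adjustment in the other. Neither item is placed above the other. The words primary and secondary are not applied to any outcome.

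The third phase is described as a "randomized field trial, superiority framework with an allocation ratio of 1:1". Its design turns on depression. At least one partner must have mild to moderate depression (Participants and setting). The pilot measures depression and stops the trial if it rises (Pilot study/feasibility). The sample size is to be calculated "considering presumed depression score reduction after the intervention, estimated sample loss, and 95% confidence level". The number of couples is still the placeholder X.

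Sampling and data collection adds an earlier time: all four scales are to be assessed "2 and 3 months after starting the intervention and compared between the groups". Data management and analysis lists t-tests, chi-square and "repeated measures analysis of variance (RM ANOVA"). ANCOVA with the enrollment score as covariate is to be used if the groups differ at enrollment. None of these tests is tied to a particular outcome.

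**The concern.** A superiority trial needs one test, or one stated rule across several tests, whose result settles the claim. Here the design points to depression, while the Outcomes section gives depression the same rank as anxiety, stress and adjustment. A reader of the results could not tell from the protocol whether an effect on, say, stress alone, with none on depression, counts as success.

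Two things are at stake. If any of the scales may carry the claim, the chance of a false claim exceeds the nominal 5%. And a sample size worked out for depression would not be tied to the hypothesis on which the trial is eventually judged. Score and change add a further choice: unless the comparison is adjusted for baseline, they are two different tests of the same effect and can disagree.

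**Working it through.** The protocol gives no family-wise error rate, power, effect size or standard deviation, so there is no figure of its own to reproduce.

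**Inputs from the protocol.** Four scales, each as score and as change (Outcomes). A 95% confidence level (Sample size), read here as a two-sided 5% level for each test. The level appears only in the sample-size sentence, and sidedness is not stated.

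**Assumed inputs.** Inter-scale correlation r from 0 to 0.9. Baseline-to-follow-up correlation ρ of 0.5 to 0.6. Equal variances at the two times. No true effect on any scale. Success claimed if any one test is significant.

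**Step 1: one test per scale (four tests).** If independent, 1 − 0.95^4 = 1 − 0.8145 = 18.5%. For correlated tests, 1,000,000 multivariate normal draws, each test rejecting at |z| > 1.96, gave:

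| r | at least one false positive |
|---|---|
| 0 | 18.6% (exact 18.5%) |
| 0.5 | 15.6% |
| 0.7 | 13.0% |
| 0.9 | 9.3% |

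That is 9.3/5 = 1.9 to 18.5/5 = 3.7 times the nominal level.

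**Step 2: score and change tested separately at 3 months (eight tests).** Without baseline adjustment, the correlation between the final score and the change is √((1 − ρ)/2). For ρ = 0.5 this is √0.25 = 0.50; for ρ = 0.6 it is √0.20 = 0.45. The simulation with ρ = 0.5 gave 22.6% at r = 0.7 and 26.8% at r = 0.5. Over ρ = 0.5 to 0.6 the range is about 23% to 27%, or 4.6 to 5.4 times 5%.

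**Step 3: direction.** These figures count false positives in either direction. Counting only false claims of benefit (nominal 2.5%), four tests gave 4.7% at r = 0.9 and 9.6% at r = 0. Eight tests with ρ = 0.5 gave 11.4% at r = 0.7 and 13.5% at r = 0.5. The multiples stay much the same.

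**Step 4: why baseline adjustment removes the score/change choice.** Let Y0 be the enrollment score, Y1 the 3-month score and G the group. If Y1 = a + bG + cY0 + error, then Y1 − Y0 = a + bG + (c − 1)Y0 + error. The group coefficient b, its standard error and its p-value are identical, so ANCOVA gives one test per scale. As written, ANCOVA is used only if the groups differ at enrollment, so this is not the default.

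**Step 5: cost of keeping four co-equal scales.** Bonferroni at 0.05/4 = 0.0125 each keeps the overall error at or below 5% (1 − 0.9875^4 = 4.9% if independent). For an illustrative effect of 0.5 SD (an assumption) with independent observations, n per arm = 2(z_α + z_power)²/0.5². At 80% power this is 8 × (1.960 + 0.842)² = 62.8, so 63, against 8 × (2.498 + 0.842)² = 89.2, so 90. That is 43% more per arm.

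**The case against.** The strongest defence is that depression is the implied primary outcome: it governs eligibility, the pilot and the sample size, and only the label is missing. A reader might infer that depression has no special standing at all. That goes too far, because it plainly has standing in the design. What remains is that the one section that defines the outcome does not carry this through.

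A second defence is that no any-scale success rule is written down, and a multiplicity procedure may sit in an analysis plan that is not shown. This stands. A reader might infer that the trial's false-positive rate is several times 5%. The protocol does not support that as a flat statement, since the inflation arises only under a rule it neither states nor excludes. The missing procedure is not the point; the unranked outcome in the protocol's own definition is.

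Third, score and change need not be two tests. With two time points, the group-by-time test in RM ANOVA is the change-score test, and ANCOVA also gives a single test. The four-test range is therefore the safer one, and the eight-test range applies only if both forms are tested separately.

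Finally, a reader might multiply by the two follow-up times and count sixteen tests, for about 37% to 44%. This is not supported. The Outcomes section names 3 months only, repeated times would naturally enter RM ANOVA, and the figure depends on an assumed correlation between the 2- and 3-month scores. Raising that correlation to 0.8 lowers it to 33% to 40%.

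**Conclusion.** The point holds in this form: the protocol fixes an unranked outcome for a superiority trial whose design rests on depression, and does not say which result decides superiority. That much follows from the text without any assumption.

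The size is conditional. It rests on an any-scale claim, on a 5% level per test inferred from the sample-size sentence, and on correlations that the protocol does not give. Under those conditions the chance of a false claim is about 9% to 18.5% with one test per scale, and about 23% to 27% with score and change tested separately at 3 months. This should be corrected, because the ambiguity concerns the trial's main claim and can be removed by wording.

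**What to change.** In Outcomes, name one primary outcome: DASS-21 depression at 3 months after the start of the intervention, compared between arms with adjustment for the enrollment score. This matches the stated basis of the sample size and makes score and change the same test. In Data management and analysis, make that adjustment unconditional for the primary comparison.

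List anxiety, stress, R-FAS and the 2-month comparisons as secondary, tested in a fixed order or by Holm, and only after depression has been shown. The error on the primary claim is then 5%.

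The change itself is a few sentences and needs no additional couples. Its real cost is that a lone effect on anxiety, stress or adjustment could no longer carry the superiority claim. If the sponsor wants all four scales to be able to carry it, the error must be controlled across them and the sample size worked out accordingly, at the price illustrated in the working.
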